### Statistical analyses

Descriptive statistics will be presented for the complete sample and separated by groups (ie, frequencies and percentages for categorical, mean, and SD or median and IQR based on the distribution). The normality of variables will be assessed visually using Q–Q plots and histograms. Demographics will be compared between asthmatics and healthy controls using unpaired Student’s t-tests (Mann-Whitney) for continuous variables and Χ^2^ (Fisher’s exact test) for categorical variables. Due to the small sample size, no imputation methods are planned a priori for missing data. Frequencies and percentages of missing will be presented, and listwise deletion will be used for concerned analyses.

We will employ an unpaired two-sample t-test (Mann-Whitney U test if non-parametric) to assess the change in FEV_1_ (primary outcome) and ACQ-5 (key secondary outcome) between visits 1 and 2 according to type 2 inflammatory status. Additionally, to assess whether the observed change in FEV_1_ within subgroups defined by type 2 high events is clinically meaningful, we will employ a Χ^2^ test to compare the proportion of patients achieving the MCID between the two groups, using an MCID of 10% relative change in FEV_1_ and 0.5 points in ACQ-5. Finally, the above results will allow for a power calculation to plan a randomised controlled trial on key outcomes.

Exploratory analyses will include an association of the outcome measures with type 2 inflammatory mediators at visit 1 using further multivariable models. To consider the influence of potentially confounding variables, simple and multiple linear regression models will be performed for both independent variables (BEC and FeNO). Covariates considered are age, sex at birth, body mass index, atopic status, serum IgE, Asian race, nasal polyposis,^21^ smoking history, Charlson index, treatment intensity at baseline, exacerbation history in the past 12 months and ACQ-5. Only confounders associated (p<0.1) with FEV_1_ will be included in the final multivariable model. A linear mixed-effects analysis of the longitudinal improvements in parameters measured at home (FeNO, peak expiratory flows and symptom scores) according to baseline FeNO and BEC.

Patient satisfaction scores, physician surveys and the percentage of tests completed during the home monitoring period will be analysed descriptively. An intraclass correlation coefficient (two-way mixed model for absolute agreement, single measures) plus Bland-Altmann fixed bias estimate for gold standard (venous BEC performed in the laboratory) versus POC (capillary BEC via SightDx OLO) will be computed with 95% CIs.

In both primary and secondary outcomes, we will explore how treatment response to OCs may be influenced by sex, gender and diversity by conducting univariable and multivariable sensitivity analyses on those factors while also controlling for the type 2 inflammatory status. We will also perform a sensitivity analysis, disaggregating all statistical outputs by sex. Results will be presented using interaction plots.

All statistics will be analysed with a two-sided α of 0.05 and, when multiple inflammatory mediators are tested, by controlling for a false discovery rate <0.05.^60^ Statistical analyses will be performed with R V.4.1.2 (R Foundation) and GraphPad Prism (GraphPad Software, USA).

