In acute asthma, several studies have documented the heterogeneity of attacks,^32–39^ with the presence of sputum inflammation characterised by elevated eosinophils^32 33 36–38^ or neutrophils.^34–38^ Importantly, these inflammatory phenotypes are indistinguishable from the point of view of initial symptoms or lung function.^38^ Other features are high BEC and elevated FeNO,^37^ increased levels of IL-8 in sputum^35 36^ or serum C reactive protein (CRP)^37^ or a different microbial flora related to FeNO values.^39^ However, treatment responses to acute systemic corticosteroid and antibiotic courses have not been related to the type 2 inflammatory phenotype and the presence of airway infection, respectively.

Concerning point-of-care (POC) measurements, it is noteworthy that capillary POC-BEC has been successfully studied in chronic airway diseases^40 41^ but not in asthma attacks; they are also approved by Health Canada and the US Food and Drug Administration (FDA).^40^ Furthermore, POC-FeNO technologies also exist, have been used for remote monitoring of FeNO, and are approved for use by Health Canada and the FDA.^41^

Finally, following the COVID-19 pandemic, we have increasing evidence supporting the relevance of early knowledge of viral and/or bacterial infection. Brendish *et al* previously showed that antibiotic use in acute airway disease dropped only once the physician had the results from the POC test, thus highlighting the importance of immediate notification of rapid multiplex testing.^31^ Improving the accessibility and affordability of POC inflammometry and microbiology testing in asthma is very likely to improve the situation for patients, physicians, manufacturers and pharmaceutical companies because it will optimise the management of the patients, identify those with type 2-driven worsening of the disease giving them better access to targeting medications and avoiding unnecessary antibiotics.^42^

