## Methods and analysis

### Study design

We planned an observational longitudinal pilot study with before/after multimodal assessments plus home monitoring (figure 1). The study will be mainly conducted at the Centre Hospitalier Universitaire de Sherbrooke’s research centre, with a secondary site to open at the Institut Universitaire de Pneumologie et Cardiologique de Québec (Québec, Canada) if needed for recruitment purposes. This is not a clinical trial; OCs are the standard treatment for asthma attacks and will be administered as required.

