### Outcome measures

#### Primary outcome

Change in the FEV_1_ between visits, with particular emphasis on a comparison based on the presence or absence of type 2 inflammatory events within the patient cohort. Specifically, we will classify type 2 high events on the basis of visit 1 BEC ≥0.15×10^9^ cells/L and/or FeNO ≥25 ppb.

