#### Secondary outcomes

Change in ACQ-5 between visits according to type 2 inflammatory status.The proportion of patients who achieve a minimal clinically important difference (MCID) ≥10% for FEV_1_ and ≥0.5 points for ACQ-5, according to the presence of type 2 high or type 2 low events.^58^ The magnitude of response will be rated as poor, moderate or good if the change is <1×, ≥1× or ≥2× the MCID values, respectively.

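### The primary FEV1 comparison between type 2 groups is not adjusted for visit 1 FEV1, and the scale of the FEV1 change is not stated

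*Protocol article*

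**What the plan says.** Statistical analyses in the protocol article names the test for the primary outcome (FEV1) and the key secondary outcome (ACQ-5): "an unpaired two-sample t-test (Mann-Whitney U test if non-parametric) to assess the change in" each of them from visit 1 to visit 2, by type 2 status. No covariate is attached.

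The design is observational: "We planned an observational longitudinal pilot study with before/after multimodal assessments plus home monitoring" (Study design). The groups come from the patients' own biomarkers: "we will classify type 2 high events on the basis of visit 1 BEC" and/or FeNO (Primary outcome).

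Table 1 schedules spirometry at both clinic visits, so visit 1 FEV1 will be available. It appears in no listed model. The exploratory regressions consider twelve covariates, ending with "treatment intensity at baseline, exacerbation history in the past 12 months and ACQ-5"; visit 1 FEV1 is not one of them. The sensitivity analyses for sex, gender and diversity control for type 2 status only.

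Primary outcome defines the endpoint as the change in FEV1 between visits, "with particular emphasis on a comparison based on the presence or absence of type 2 inflammatory events within the patient cohort", without saying whether the change is in litres or percent. Statistical analyses does not say so either when it names the test. Sample size uses a difference of 10 with an SD of 10, in percent, and the responder threshold is a 10% relative change.

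**The concern.** How much FEV1 recovers in a week is likely to depend on where the patient starts. A patient with a low value on day 0 has more room to improve and, through regression to the mean, tends to measure higher next time. Entry is based on symptoms with no FEV1 limit (Participants), and the Discussion expects mild to severe asthma, so visit 1 FEV1 should vary widely.

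Nothing in the design balances visit 1 FEV1 between the groups. If it differs, part of the observed difference in response reflects the starting point and not the inflammatory phenotype. If it does not differ, omitting it leaves explainable variance in the error term. Either way the result matters beyond this study, because Statistical analyses says it will feed the power calculation for a randomised trial.

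The unstated scale is a separate gap. The sample size is tied to percent change, but the endpoint definition does not bind the analysis to it.

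**Working it through.** **Inputs from Sample size:** two-sided alpha 0.05, ratio 1:1, difference 10 and SD 10 (percent), 90% power, n=46, with 50 targeted.

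**Assumed, because the documents do not give them:** r, the within-group correlation of FEV1 change with visit 1 FEV1 (0.2 to 0.5); D, the difference in mean visit 1 FEV1 between groups in within-group SDs (0 to 1); and a 40:10 split. The split applies the 80% type 2 high share that the Discussion gives for severe asthma to n=50. The Discussion expects a lower share in milder disease.

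**Step 1. The plan's own figure.** Exact noncentral t power for difference 10 and SD 10 is 89.97% at 22 per group (n=44) and 91.25% at 23 per group (n=46). So 46 is the smallest equal-group total reaching 90%, and the stated figure reproduces.

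**Step 2. Precision if baselines match (D=0).** With visit 1 FEV1 in the model, the residual SD is 10 × √(1 − r²) and one degree of freedom is lost.

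| r | Residual SD | Power, 23:23 | Power, 40:10 |
|---|---|---|---|
| unadjusted | 10.00 | 91.2% | 79.1% |
| 0.2 | 9.80 | 92.3% | 80.7% |
| 0.3 | 9.54 | 93.5% | 82.7% |
| 0.5 | 8.66 | 96.9% | 89.2% |

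**Step 3. Shift if baselines differ.** The part of the unadjusted difference explained by visit 1 FEV1 is |r| × SD of change × D = |r| × 10 × D points.

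- r=0.3, D=0.5: 0.3 × 10 × 0.5 = 1.5 points
- r=0.5, D=0.5: 0.5 × 10 × 0.5 = 2.5 points
- r=0.5, D=1: 0.5 × 10 × 1 = 5 points
- D=0: zero

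Suppose there is no true difference between patients with the same visit 1 FEV1. At 23:23 the unadjusted test then rejects 7.9%, 13.2% and 38.2% of the time in the first three cases, instead of 5%.

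**Step 4. The price of adjusting when baselines differ.** At 1:1 the variance of the adjusted difference is multiplied by 1 + D²/4. Power at 23:23, against 91.2% unadjusted:

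| r | D=0.5 | D=1 |
|---|---|---|
| 0.3 | 92.1% | 87.4% |
| 0.5 | 96.0% | 92.8% |

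Adjustment usually gains power, but it loses some when the imbalance is large and r is modest.

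**The case against.** - **The change may not be raw.** A reader might infer that the test ignores visit 1 FEV1 altogether. The documents do not support that: Sample size and the responder threshold point to percent change, which has visit 1 FEV1 as its divisor. This stands. Dividing by baseline is not adjusting for it, however, and the endpoint definition still leaves the scale open.
- **Bias needs a systematic baseline difference.** The Introduction reports from earlier work that "these inflammatory phenotypes are indistinguishable from the point of view of initial symptoms or lung function". If that carries over, D is near zero and only precision is at issue. This limits the claim but does not settle it, since the statement concerns sputum phenotypes and not groups defined by blood eosinophils and FeNO.
- **Chance imbalance is not an extra error.** A reader might count it as one, especially with a small group. It is already within the t-test's standard error, so counting it again would count the precision loss twice. This stands.
- **Adjustment is not free and not a cure.** Step 4 shows that it can cost power. In non-randomised groups the adjusted and change-score analyses can answer different questions (Lord's paradox), and a linear baseline term does not abolish a ceiling effect. All of this stands, and it argues for showing both analyses.
- **Other details.** A reader might also fault the unnamed pre- or post-bronchodilator value or the Mann-Whitney fallback. The first is commonly left to a fuller document that is not shown here, and the second is conventional. Neither is part of this point.
- **It is a pilot.** The Discussion already names reliance on FEV1, the observational design and the small sample as limitations. That lowers the stakes, but the change needs only wording.

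**Conclusion.** The point holds in a limited form. The primary and key secondary comparisons are unadjusted for baseline, visit 1 FEV1 is collected but is in no listed model, and the scale of the primary change is not stated although the planning figures are in percent.

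The consequence depends on r and D. With matched baselines, adjustment adds about 1 to 6 percentage points of power at n=46 for r from 0.2 to 0.5, and about 2 to 10 points at an assumed 40:10 split. With a half-SD baseline difference and r of 0.3 to 0.5, 1.5 to 2.5 of the 10 targeted points would come from visit 1 FEV1.

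The documents do not show that the groups will differ at baseline, so bias is possible but not demonstrated. The sample size calculation is correct for the test it names.

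**What to change.** 1. State under Primary outcome and Statistical analyses that the primary change in FEV1 is relative (percent), as in Sample size.
2. Make the primary analysis a linear model of log visit 2 FEV1 on type 2 status and log visit 1 FEV1. Back-transform the type 2 coefficient to a percent difference with a 95% CI.
3. Analyse visit 2 ACQ-5 on type 2 status and visit 1 ACQ-5 in the same way, untransformed.
4. Keep the planned unadjusted comparison of change as a fixed sensitivity analysis, and report both results whatever they show, with a sentence on what each estimates.

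The back-transformed result is a ratio, which is close to a difference in percent change but not identical. For example, assumed mean changes of 20% and 10% give 1.20/1.10 = 1.09.

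Cost: wording and one degree of freedom, with no new data and no change to n. The downsides are some loss of precision if baselines differ greatly and r is small, two estimates that may diverge, and ceiling effects that are reduced but not removed.

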**Methods and analysis:**

An observational longitudinal pilot study with multimodal clinical and translational assessments will be performed on 50 physician-diagnosed ≥12-year-old asthmatics presenting with an asthma attack and 12 healthy controls, including blood eosinophil count (venous and point-of-care (POC) capillary blood), FeNO and testing for airway infection (sputum cultures and POC nasopharyngeal swabs). People with asthma will be assessed on day 0 and after a 7-day corticosteroid course, with home monitoring performed in between. The primary analysis will be the change in the forced expiratory volume in 1 s according to type 2 inflammatory status (blood eosinophils ≥0.15×10^9^/L and/or FeNO ≥25 ppb) after treatment. Key secondary analyses will compare changes in symptom scores and the proportion of patients achieving a minimal clinically important difference. Exploratory analyses will assess the relationship between clinical, lung function, inflammatory and microbiome parameters; satisfaction plus reliability indices of POC tests; and sex–gender variability in treatment response. Ultimately, this pilot study will serve to plan a larger trial comparing the clinical and biological response to systemic corticosteroids according to inflammatory biomarkers, offering valuable guidance for more personalised therapeutic strategies in asthma attacks.

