The treatable trait success story of chronic asthma certainly makes a case for the reappraisal of our approach to acute asthma.^6 7 43^ Is it time for precision medicine to attack the problem of asthma attacks? A worthwhile question, considering that corticosteroid toxicities appear after the lifetime equivalent of only four bursts (≥1000 mg cumulative dose) of prednisone—that is, four severe asthma attacks^44^—and the increasing levels of resistance to antibiotics observed, mainly due to inadequate prescriptions.^7 29^ Biomarker-guided management could avoid harm to individual patients and society stemming from the inappropriate use of OCs and/or antibiotics due to overuse or without proper consideration of their potential risks and side effects.^44 45^ Simply stated, corticosteroid and antibiotic stewardship can and should be assisted by acute POC testing.

Based on previous knowledge from chronic stable asthma and reports that asthma attacks are heterogeneous events, we hypothesise that treatment responses to OCs in acute asthma vary according to the underlying inflammatory phenotype. Specifically, we speculate that events identified by raised BEC and/or FeNO benefit most from OCs and that events presenting with low type 2 biomarkers have a lesser objective clinical and biological anti-inflammatory response but perhaps higher rates of airway infection or dysfunction. If this proves to be the case, we will be in a solid position to move forward with a randomised clinical trial comparing biomarker-directed OC use with the current ‘one-size-fits-all’ approach. An important secondary hypothesis of our study is that POC inflammatory and microbiological assessments in acute asthma are possible, acceptable and reliable. The ramifications of such findings would be to plan a clinical trial assessing biomarker-guided asthma attack management in primary care.

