### Participants

People ≥12 years old with physician-diagnosed asthma since >6 months experiencing an asthma attack as defined by GINA (episode characterised by a progressive increase in symptoms of shortness of breath, cough, wheezing or chest tightness that represent a change from the patient’s usual status)^2^ with a patient and/or physician decision to initiate a burst of OCs (but not yet started) will be assessed within 24 hours on weekdays after a screening telephone call. Exclusion criteria are a SARS-CoV-2-positive event, asthma treated with a monoclonal antibody or maintenance OCs, current smoking, significant overlapping cardiopulmonary disease (including chronic obstructive pulmonary disease, defined as age >40 years old AND persistent airflow limitation with forced expiratory volume in 1 s (FEV_1_)/forced vital capacity <0.7 AND >10 pack-year smoking history or α-1-antitrypsin deficiency), a confounding immunological state, ongoing pregnancy or contraindication to corticosteroids.

Although we will assess asthmatics with a history of physician-diagnosed asthma, patients included in the primary analysis and counting toward the target sample size will need to have objective proof of asthma as defined by international guidelines^2^ either based on the medical record or with a clinically required follow-up test ordered by the study respirologist and performed after study participation. Unconfirmed asthmatics data will be reported but not used for the primary analysis.

Non-atopic, non-smoking healthy volunteers with normal spirometry and no history of lung disease will form the control cohort. All participants (±their parent or legal tutor) must provide informed consent for the study protocol. Patients who cannot or refuse to participate in the diary card data collection for the home monitoring period will still be able to participate in all other study procedures.

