### Study visits

Visit 1 will be on day 0 of the asthma attack, with oral prednisone issued by the community pharmacy (40 mg×7 days) (figure 1). Concomitant antibiotic use will only be considered for patients with ≥1 of the following criteria: CRP >20 mg/L, procalcitonin >0.25 µg/L (when available), or positive sputum culture and/or multiplex POC test for a significant bacterial pathogen. Healthy controls will attend only visit 1. Multimodal assessments performed at study visits lasting ~2 hours are detailed in table 1. In visit 1, these comprise:

Medical history and examination, including vital signs, inhaler technique and adherence check (using prescription refills of community pharmacy), five-item Asthma Control Questionnaire (ACQ-5),^46 47^ dyspnoea rated on the modified Medical Research Council Scale,^48^ Visual Analogue Scale for respiratory symptoms, Pittsburgh Vocal Cord Dysfunction Index,^49^ Nijmegen Questionnaire,^50^ Hospital Anxiety and Depression Scale,^51^ chest X-ray.FeNO measurement (NIOX VERO, Circassia) and pre/post-bronchodilator oscillometry (Tremoflo C-100, Thorasys Thoracic Medical Systems) and spirometry plus peak expiratory flow.Peripheral blood tests (complete blood count with differential, serum CRP, total and specific serum IgE, biobank), POC-BEC (Sight OLO, Sight Diagnostics), urine sample (creatinine, biobank), nasosorption with nasal epithelial lining fluid (NELF), nasal swab for the ultrarapid ID NOW (Abbott Industries) SARS-CoV-2 molecular test, nasopharyngeal swab for rapid multiplex PCR using the BIOFIRE Respiratory 2.1 (RP2.1) Panel (bioMérieux). If no spontaneous sputum is available, following negative COVID-19 testing and post-bronchodilator FEV_1_ > 60% predicted value or >1.5 L, induced sputum collection with hypersaline nebulisation would then be performed, as done in a previous asthma attack study.^37^

**Table 1 T1:** Study visit overview

Visit	Screening	0	1–6	7	97
Location	Telephone	Clinic	Home	Clinic	Virtual±telephone
Consent	Given	Signature			
Inclusion/exclusion criteria overview	x	x			
SARS-CoV-2 test (ID NOW)		x		x	
Medical history		x		x	x
Physical examination by doctor		x			
Inhaler technique check		x			
Adherence check (call to community pharmacy)		x			
Check if patient picked up prednisone tablets			x		
Review of test results by doctor				x	±
Questionnaires					
Medical Research Council dyspnoea scale		x		x	
Asthma Control Questionnaire (5 items)		x	x	x	x

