## Discussion

The proposed observational and translational before/after pilot study of asthma attacks across the range of asthma severities will be the first to focus on the role of BEC and FeNO and explore the clinical and biological factors affecting OC treatment response in acute asthma. We view our pilot study of POC measurements for assessing type 2 inflammation and airway infection as a stepping stone to plan a clinical trial allowing for biomarker implementation in the primary care setting. Biomarker-guided management could avoid harm to individual patients and society stemming from inappropriate use of OCs and/or antibiotics.

We expect events identified by raised BEC and/or FeNO to benefit most from corticosteroids, and POC tests to be useful theragnostic and mechanistic tools. Specifically, we expect increased BEC and FeNO to predict greater improvements in (a) FEV_1_ (primary outcome), (b) ACQ-5 scores (key secondary outcome), and (c) inflammatory mediators, symptoms, and other physiological aspects (exploratory outcomes). If the study hypothesis is confirmed—a phenotypical variability in treatment responses associated with type 2 airway inflammation—then the utility of BEC and FeNO could be studied to manage asthma attacks in a randomised controlled trial.

Three distinct studies in asthma attacks are underway, each with its unique objectives. ExCluSie-F (Phenotyping and Classifying Asthma Exacerbations; NCT05304039) is a prospective cohort that will explore the association between phenotypical characteristics and a composite outcome of treatment effectiveness. On the other hand, ‘APEX’ (Asthma: Phenotyping Exacerbations; NCT04293588) is a longitudinal cohort with participants who have experienced at least one asthma exacerbation in the previous year that aims to assess the proportion of patients displaying eosinophilic and non-eosinophilic phenotypes. Lastly, ‘BOOST’ (Recovery of Breakthrough Asthma Attacks Treated with Oral Steroids While on Monoclonal Antibody Therapy) is a prospective observational study involving adults on long-term biological treatment for asthma that will compare clinical recovery between individuals with high FeNO levels during their asthma attacks and those with low FeNO.^63^

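### With every attack treated with oral corticosteroids, the type 2 contrast shows who recovers more on treatment, not who benefits more from it, and should not serve as the treatment effect for the next trial

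*Protocol article*

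**What the plan says.** **Design.** Study design states: "This is not a clinical trial; OCs are the standard treatment for asthma attacks and will be administered as required". Under Participants, patients are eligible "with a patient and/or physician decision to initiate a burst of OCs (but not yet started"). Study visits has a 7-day prednisone course issued at visit 1. The Abstract gives the timing: "People with asthma will be assessed on day 0 and after a 7-day corticosteroid course". The only comparison group outside the asthma cohort is 12 healthy volunteers, and "Healthy controls will attend only visit 1".

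**Analysis.** Primary outcome and Statistical analyses compare the change in FEV1 between visits in type 2-high and type 2-low events, by an unpaired t-test or Mann-Whitney test. Both sections word this neutrally.

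**Reading of the result.** The Introduction's hypothesis is that "events identified by raised BEC and/or FeNO benefit most from OCs". The Discussion says: "We expect events identified by raised BEC and/or FeNO to benefit most from corticosteroids". In its paragraph on pitfalls, the Discussion also expects to detect corticosteroid responsiveness that varies with the biomarkers.

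**Use of the result.** Statistical analyses: "Finally, the above results will allow for a power calculation to plan a randomised controlled trial on key outcomes". The Introduction describes the next step as "a randomised clinical trial comparing biomarker-directed OC use with the current" uniform approach. Elsewhere the Discussion mentions a placebo-controlled trial, and the Abstract a larger trial comparing response to corticosteroids by biomarker.

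**Limitations.** The Discussion lists the unknown type 2 ratio, the reliance on FEV1, recent OC use, and the observational design with a small sample. Natural recovery and the lack of an untreated comparator are not mentioned.

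**The concern.** To say that one group benefits more from a treatment is to compare each group's outcome on treatment with its outcome off treatment. Here no attack is observed off treatment. The data can show that type 2 status is prognostic among treated patients. They cannot show that it predicts the effect of OCs.

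The protocol's own expectations make the distinction a practical one. The Introduction suggests that type 2-low events may involve more airway infection or dysfunction. Study visits ties antibiotic use to CRP, procalcitonin or a bacterial finding. The two groups may therefore differ in the cause of the attack and in co-treatment, and so in recovery, whatever OCs do. Concomitant antibiotics are not among the listed covariates. Even if they were, adjustment could not supply the missing untreated course.

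Two things are at stake: a primary conclusion worded more strongly than the design allows, and a follow-on trial that could be sized on a quantity that is not its treatment effect.

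**Working it through.** **1. The plan's own figure.** Inputs from Sample size: difference 10%, SD 10%, ratio 1:1, two-sided α 0.05, power 90%. The standardised difference is 10/10 = 1.0.

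- Normal approximation: n per group = 2 × (1.960 + 1.282)² / 1.0² ≈ 21.0, rounded up to 22, total 44.
- Exact t-test: 22.02 per group, rounded up to 23, total 46, with power 0.912.

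The stated n=46 reproduces. Nothing below changes it.

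**2. What the contrast contains.** For each phenotype, observed change = R + E. R is the change that would occur without OCs (spontaneous recovery, regression to the mean, other care), and E is the OC effect. Then

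observed contrast = (E_high − E_low) + (R_high − R_low).

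The study estimates only the left-hand side. Suppose the observed changes are +15% (high) and +5% (low), values assumed so as to match the planned 10-point difference:

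| Assumed R, high / low | Implied E, high / low | OC benefit larger in |
|---|---|---|
| 0 / 0 | +15 / +5 | type 2-high |
| +10 / 0 | +5 / +5 | neither |
| +15 / −5 | 0 / +10 | type 2-low |

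The same data fit all three rows. In the second, 23 per group would still give about 91% power to find the contrast although there is no differential OC effect.

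**3. Consequence if the contrast were used as an OC effect.** The documents give no natural-recovery figure, so a range is assumed. Let N be the part of the 10 points due to differential natural recovery, keep the SD at 10%, and take the OC effect in type 2-low events as zero. The OC effect in type 2-high events is then 10 − N. For a two-arm comparison with effect 10 − N (normal approximation):

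| N | 10 − N | Total for 90% power | Power with 22 per arm |
|---|---|---|---|
| 0 | 10 | 44 | 0.91 |
| 2.5 | 7.5 | 76 | 0.70 |
| 5 | 5 | 170 | 0.38 |
| 7.5 | 2.5 | 674 | 0.13 |

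**4. A biomarker-directed trial.** If the arms differed only in whether type 2-low events receive OCs, the between-arm difference would be (type 2-low share) × (OC effect in type 2-low events). Assume a 5-point effect. With a share of 50% (the 1:1 ratio in Sample size) the difference is 0.5 × 5 = 2.5 points. With 20% (the complement of the roughly 80% type 2-high that the Discussion gives for severe asthma) it is 0.2 × 5 = 1.0 point. At SD 10% and 90% power, the exact t-test needs 337.2 and 2,102.4 per arm, so 338 and 2,103, against 23 per arm for a 10-point difference. This assumes a superiority comparison on FEV1, which the protocol does not specify.

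**The case against.** The strongest reply is that this is a pilot, expressly not a clinical trial. The hypothesis is worded as speculation and expectation, and the proposed next step is randomisation, which is the right way to separate prognostic from predictive effects. OCs are standard care, so a single treated cohort is an open and reasonable choice. All of this stands. It is why the remedy is wording and not an untreated arm. It does not cover the inference itself: calling the study observational and small does not tell the reader that natural recovery is mixed into the contrast. The caveat in Sample size about needing confirmation applies to secondary and exploratory outcomes, not to the primary one.

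Four stronger readings are tempting, and the document does not support them:

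- *The protocol commits to sizing the next trial on the between-phenotype difference.* The sentence in Statistical analyses does not say which results will be used. The results described there also yield SDs, group proportions and missing-data rates, which are legitimate inputs.
- *The next trial will withhold corticosteroids from some patients.* That is a fair inference from the Introduction and from the placebo-controlled option in the Discussion. The sentence on the power calculation says only that the trial is randomised, and for a comparison of response by biomarker, as the Abstract describes, the measured contrast is directly relevant.
- *A positive result would be taken to justify withholding OCs.* No section says so. The Discussion says that biomarker utility could then be studied in a randomised trial.
- *The primary outcome and its test are mis-stated.* Both are neutrally worded and need no change.

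**Conclusion.** The point holds in a limited form. Because all attacks are treated, the primary contrast estimates a difference in 7-day recovery under OCs. The statements of greater benefit in the Introduction and Discussion, and the Discussion's phrase about corticosteroid responsiveness, go beyond what the design can show, and no listed limitation says so. The sentence on the power calculation leaves room for the contrast to be used as a treatment effect, but does not say that it will be.

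The size cannot be fixed from the document. The trial totals of 44 to 674, the power of 0.91 to 0.13, and the 338 and 2,103 per arm rest on assumed recovery shares, assumed OC effects and an assumed trial design. They show how sensitive planning would be and are not estimates. The study's n=46, endpoint and test are unaffected. This should be corrected, but it does not invalidate the study.

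**What to change.** 1. **Introduction and Discussion (hypothesis, expected result, and the phrase on corticosteroid responsiveness).** State the testable hypothesis and the permitted conclusion as: *recovery over 7 days in OC-treated attacks differs by type 2 status.*
2. **Discussion, limitations.** Add: *without an untreated comparator, the study cannot show differential OC benefit, or lack of benefit in type 2-low events.*
3. **Statistical analyses, sentence on the power calculation.** List what will be taken from this study: the SD of FEV1 and ACQ-5 change, the proportion of type 2-low events, the completion rate, and the OC-treated course of type 2-low events. State that the between-phenotype difference will not be used as the OC treatment effect for a biomarker-directed or placebo-controlled trial, and that this effect or margin will be justified from outside this study.

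Any sample-size illustration for the later trial should be labelled as resting on assumptions.

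The cost is a few sentences and a more modest claim. No new patients, data or analyses are needed.
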